### Power calculations

A random sample of 517 patient sets of X-ray and radiology reports, proportional to fractures admitted to hospital with fractures managed in the ED or short stay unit, will be selected for classification by an orthopaedic surgeon, to quantify the agreement between the AI techniques and human assessment [35]. This is based on the diagnostic test with a null hypothesis of 0.7, alternative hypothesis of 0.8, power>0.8 and prevalence of dorsal displacement type fractures of 30% [36]. Class probabilities from the fracture classification will be generated and compared with orthopaedic surgeon assessment of the images and reports (gold standard). Key fracture words/phrases in text and regions in images, correlated with the predictions, will be highlighted with attention weights using a visualisation interface for surgeons to review the results generated by the models. We will retain 20% of the collected visual-linguistic fracture data pairs from training to test the proposed models. More than 6,000 VOTOR and 4,000 ED only cases will be available for the study, making the sample size more than sufficient to meet aim 2 of the study.

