### Aim 2: Prediction modelling

The performance of models including the AI predicted indicators from the deep learning models will be tested against models including standard registry information using the linked VOTOR registry data (data source 4)). The capacity of the AI indicators to predict outcomes of clinical and post-operative complications, and PROMs post-injury. This will enable us to determine which radiological features based on the X-rays and text reports improve prediction over the standard data available in the registry. AI-derived fracture predicted probabilities and classes will be added to the VOTOR registry data and sent to the CVDL for the Linked VOTOR data. This linked dataset will provide a comprehensive longitudinal dataset for the prediction models.

The capacity of the AI derived fracture characteristics to predict outcome compared to the Linked VOTOR registry data alone will be tested using the following outcomes:

Fracture management complications: implant failure; non-union; mal-union of the fracture; infection; neurological injuryReadmission to hospital for fracture managementPresentation to the ED for fracture-related issuesPatient-reported outcomes at 6-, 12-, and 24-months after injury: EQ-5D-5L; 12-item WHODAS; pain scores; return to work and work-related disability.

A systematic approach to variable selection and model predictive performance will be implemented (Fig 1). Models will investigate predictive pathways and risk of outcomes of interest. State of the art longitudinal machine learning (ML) models [44] will be used for both the variable selection and prediction stages. The large number of covariates raise potential multicollinearity issues, and the possibility of unstable estimates. Therefore, where applicable a number of ML penalized regression methods will be implemented to reduce covariate numbers. The analyses will account for correlated and clustered responses to perform the variable reduction and prediction tasks.

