Linear and generalized linear mixed models (LMMLasso/GLMMLasso) [45], longitudinal multi-level factorization machines model (LMLFMM) [46], longitudinal support vector regression (LS-SVM) [47] and mixed effects random forest (MERF) [48] will be used as these machine learning techniques can handle longitudinal data and a large number of potentially correlated features. The inclusion of predictions from Aim 1 will incorporate associated error that potentially compounds further error with their inclusion in the predictive models, so we will use several measures to review model performance. All models will be summarised by the predictive performance measures of accuracy, precision and recall [49] to select the best performing model for each outcome, and quantify the impact of the inclusion of the AI variables over registry data alone.

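### Aim 2 selects models and measures the AI gain by accuracy, precision and recall at an unstated cut; at a 0.5 cut these are almost insensitive to better risk prediction for outcomes at about 5% or below

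*Protocol article*

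**What the plan says.** The Aim 2 section of the protocol article states its target as risk: "Models will investigate predictive pathways and risk of outcomes of interest". Its outcomes include several yes/no events: five fracture-management complications, readmission, and return to the emergency department for the fracture. No event rate is given for any of them.

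The same section then fixes how the models are judged: "All models will be summarised by the predictive performance measures of accuracy, precision and recall [49] to select the best performing model for each outcome". The sentence goes on to give the same measures a second task, to "quantify the impact of the inclusion of the AI variables over registry data alone". That second task is the question posed by Aim 2.

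The visible text names no cut on the predicted risk, no measure of discrimination across cuts, no calibration measure and no proper score.

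**The concern.** Accuracy, precision and recall all come from one two-by-two table, which exists only after each predicted risk has been turned into a yes or a no. A model that moves a patient's risk from 3% to 15%, correctly, gains nothing in that table if the cut is 50%.

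For an uncommon complication, few or no patients have a predicted risk above one half. Accuracy then sits at the share of patients without the event. Recall is near zero, and precision is undefined or rests on a handful of flagged patients. A real improvement from the AI variables could be reported as none.

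If the cut is lowered to obtain usable recall, the result depends on where it is placed, and the text leaves that open. Miscalibrated risks would go unseen at any cut. This matters because the section itself warns that error in the Aim 1 predictions may carry into the Aim 2 models.

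**Working it through.** **Plan's own figures.** There is none to reproduce for Aim 2. The only computed sample size, 517 under Power calculations, belongs to Aim 1. It reproduces with an exact binomial test at two-sided 0.05 (155 / 0.30 = 517) and does not bear on this point.

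**Inputs from the document.** The three measures and their two uses (Aim 2 section); the number of cases, "More than 6,000 VOTOR and 4,000 ED only cases will be available for the study", of which the 6,000 registry cases feed Aim 2.

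**Assumptions, not in the document.** Event rates p of 2%, 5% and 10%; a cut t of 0.5 or, alternatively, t = p; AUC 0.70 for registry data alone and 0.75 with AI; perfectly calibrated risks.

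**Model.** A score x is N(0,1) in patients without the event and N(d,1) in those with it.
- d = √2 · Φ⁻¹(AUC), giving 0.742 for AUC 0.70 and 0.954 for AUC 0.75.
- Calibrated risk = expit(logit p + d·x − d²/2).
- A patient is flagged when x > c, with c = (logit t − logit p + d²/2) / d.
- Recall = 1 − Φ(c − d); false-positive rate (FPR) = 1 − Φ(c).
- Accuracy = p·recall + (1 − p)(1 − FPR).

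**Worked case: p = 5%, AUC 0.75, t = 0.5.** c = (0 + 2.944 + 0.455) / 0.954 = 3.564. Recall = 1 − Φ(2.610) = 0.0045. FPR = 1 − Φ(3.564) = 0.00018. Accuracy = 0.05 × 0.0045 + 0.95 × 0.99982 = 0.9501. Flagged = 6,000 × (0.05 × 0.0045 + 0.95 × 0.00018) ≈ 2.4 patients.

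**Cut 0.5, without AI → with AI:**

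| Event rate | Accuracy, no model | Accuracy | Recall | Flagged of 6,000 |
|---|---|---|---|---|
| 2% | 0.9800 | 0.9800 → 0.9800 | 0.0000 → 0.0002 | below 0.1 in both |
| 5% | 0.9500 | 0.9500 → 0.9501 | 0.0002 → 0.0045 | 0.1 → 2.4 |
| 10% | 0.9000 | 0.9001 → 0.9009 | 0.005 → 0.034 | 5 → 35 |

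A larger step, AUC 0.70 to 0.80, shows the same pattern. At 5% events accuracy goes from 0.9500 to 0.9505 and recall from 0.0002 to 0.030, while the scaled Brier score triples (0.031 to 0.097).

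**How often the gain is detected** (simulated nested models, AUC 0.70 to 0.75, all 6,000 patients scored, cut 0.5; paired tests):

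| Event rate | Accuracy | Recall | Log score |
|---|---|---|---|
| 2% | 0% | 0% | about 90% |
| 5% | at most 1% | at most 4% | about 100% |
| 10% | about 12% | over 99% | 100% |

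**Cut at the event rate.** Now logit t = logit p, so c = d/2. Recall and specificity both equal Φ(d/2), and so does accuracy, whatever the event rate: 0.645 without AI and 0.683 with it. Precision at 5% events goes from 0.087 to 0.102. Flagging nobody scores 0.950 on accuracy at 5% events, so accuracy puts both models well below a rule with no predictive content.

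**The case against.** A reader might infer that the three measures cannot register better prediction, or that good models flag nobody. The documents do not support either as a general statement.

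- **Event rates are assumed.** None is given. Readmission or return to the emergency department may exceed 10%, and at 10% recall detects the gain in over 99% of runs even at a 0.5 cut. A strong model also flags patients at lower rates: with AUC 0.90 at 5% events, about 103 of 6,000 are flagged and recall is 0.24.
- **The 0.5 cut is assumed.** With the cut at the event rate, precision and recall both move, and accuracy separates the two models in every run. Recall alone is weak there, detecting the gain in 18% of runs at 2% events and 30% at 5%.
- **The log-score comparison is a best case.** It scores known, calibrated risks on all 6,000 patients. The article says "We will retain 20% of the collected visual-linguistic fracture data pairs from training to test the proposed models", which concerns Aim 1. If the same share were held out in Aim 2 (0.20 × 6,000 = 1,200), log-score detection would fall to about 30% at 2% events and 60% at 5%.
- **This is a condensed article.** Its analysis-plan figure and any separate analysis plan are not shown. The absence of discrimination and calibration measures can be asserted only of the visible text, and leaving the threshold to a later document is not in itself a fault.

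The first three limit the size and reach of the effect. The fourth does not remove the point: the article does state which measures decide, and that stated choice fits the risk aim badly.

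**Conclusion.** The point holds in conditional form. The Aim 2 section gives model choice and the AI gain to three measures that ignore predicted risk and depend on an unstated cut. If a binary outcome occurs in about 5% of patients or fewer and the cut is 0.5, all three are almost insensitive to a gain from AUC 0.70 to 0.75. The effect is near total at 2%, strong at 5%, and fades from about 10%, where recall registers the gain and accuracy mostly does not.

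Accuracy is a poor deciding measure at either cut. At 0.5 it barely differs from having no model; at the event rate it ranks both models below flagging nobody (0.645 and 0.683 against 0.950 at 5% events). Precision and recall are usable, but only at a chosen threshold, and the result depends on that choice. The figures rest on assumed event rates, AUCs and calibrated risks, and the point concerns the binary outcomes only.

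**What to change.** Revise the performance sentence in the Aim 2 section for the binary outcomes:

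- Select models and quantify the AI gain by AUC together with a Brier or log score, and report calibration (slope and plot).
- Give the difference between registry-only and registry-plus-AI models with a paired confidence interval.
- Keep precision and recall as secondary measures, at a risk threshold fixed in advance for each outcome.
- Drop accuracy as a deciding measure.

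The cost is a change of wording and standard software output; no new data are needed. The results are less simple to quote than a percentage correct. With a small evaluation set, for example 1,200 patients, even the log score may miss a modest gain for a rare outcome, so the interval should be reported and a null result read with that in mind.

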### Data sources

The PRAISE study will use four data sources: 1) VOTOR registry patient data; 2) ED patient data; 3) SSU patient data; and 4) linked VOTOR patient data. Data sources 1) to 3) will be used to achieve study aim 1) and data source 4) will be used to achieve study aim 2).

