#### 3) Linked VOTOR data

The VOTOR registry data and data generated from the AI models in aim 1) for VOTOR cases will be sent to the Centre for Victorian Data Linkage (CVDL) for linkage with the Victorian Admitted Episodes Dataset (VAED) and the VEMD to provide admissions and ED presentations for the two years prior, and all admissions and ED presentations in the two years following, the VOTOR admission. This linked dataset will provide a comprehensive dataset for the prediction models, and will contain detailed descriptors of the fracture including fracture pattern, soft tissue injury and treatment, as well as demographic details, pre-existing health conditions, injury event details, treating healthcare service, and associated injuries.

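### Most Aim 2 patients would carry AI indicators from a network trained on those same patients, and the stated response to Aim 1 error cannot show or remove this

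*Protocol article*

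**What the plan says.** Four places in the protocol article have to be read together.

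- **Data sources.** "Data sources 1) to 3) will be used to achieve study aim 1", and the first of these sources is the VOTOR registry; "data source 4) will be used to achieve study aim 2", which is the linked VOTOR data. The same VOTOR patients therefore serve both aims.
- **Power calculations.** "We will retain 20% of the collected visual-linguistic fracture data pairs from training to test the proposed models". The unit is the pair, and no allocation by patient or by source is given. On numbers: "More than 6,000 VOTOR and 4,000 ED only cases will be available for the study".
- **3) Linked VOTOR data, and Aim 2.** "data generated from the AI models in aim 1) for VOTOR cases will be sent" for linkage, and "AI-derived fracture predicted probabilities and classes will be added to the VOTOR registry data". Neither sentence restricts this to held-out cases.
- **Aim 2: Prediction modelling.** The text grants that error in the Aim 1 predictions may compound in the outcome models, "so we will use several measures to review model performance". The measures named are accuracy, precision and recall. They also choose the best model for each outcome and quantify what the AI variables add.

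**The concern.** A network's output for a patient it was trained on does not have the same error as its output for a new patient. It is usually closer to the training label and more confident. If most Aim 2 patients are scored in-sample, the AI variable in the outcome models is a cleaner measurement than a hospital would obtain from the deployed system, and its error differs between trained and untrained patients in the same dataset.

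The Aim 2 result is the added value of the AI variables over registry data, and Aim 3 is to deploy the algorithms. The quantity of interest is therefore the gain in patients the network has never seen. Accuracy, precision and recall are all computed on the same indicators, so any optimism is common to all three. A hold-out made inside Aim 2 does not help, because those held-back patients also carry mostly in-sample scores.

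**Working it through.** **1. The plan's own figure.** The only computed sample size is 517 sets, from 0.7 against 0.8, power above 0.8 and prevalence 30%. An exact one-sample binomial test (two-sided 0.05 assumed, since alpha is not stated) needs 155 cases: reject at 120 or more, upper-tail error 0.0247, power 0.818. Then 155 / 0.30 = 516.7, which rounds up to 517. The figure reproduces. It is used here only as the source of the 0.80 and the 30% below.

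**2. Share of VOTOR patients used in training.** The inputs are 6,000 VOTOR cases, 4,000 ED cases and a 20% hold-out. Short-stay numbers are not given separately, so these two groups are taken as the whole pool.

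- Hold-out size: 0.20 × 10,000 = 2,000.
- Proportional split by patient: 0.80 × 6,000 = 4,800 trained (80%), and 1,200 held out.
- All 2,000 held-out cases from VOTOR: (6,000 − 2,000) / 6,000 = 67% trained.
- All held-out cases from ED: 100% trained, no VOTOR case held out.
- Split by pair: a patient with k pairs has at least one in training with probability 1 − 0.2^k, which is 96% for k = 2 and 99% for k = 3.

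**3. Possible size of the inflation.** Take a binary feature with prevalence p = 0.30, and let a be the sensitivity and specificity (assumed equal) of the AI class. The proportion of AI-positives is q = p·a + (1 − p)(1 − a). The share of the feature's explained variance that the AI class carries is

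phi² = p(1 − p)(2a − 1)² / [q(1 − q)].

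This treats the feature as independent of the registry covariates. At a = 0.80, q = 0.38 and phi² = 0.21 × 0.36 / 0.2356 = 0.321. At 0.90 it is 0.599 and at 0.98 it is 0.908.

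With 80% of patients scored in-sample and 20% at 0.80, the pooled accuracy is m = 0.8·a_in + 0.16, and the inflation is phi²(m) / phi²(0.80):

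| Assumed in-sample accuracy | Pooled m | phi² at m | Ratio to 0.321 |
|---|---|---|---|
| 0.80 | 0.800 | 0.321 | 1.0 |
| 0.82 | 0.816 | 0.358 | 1.1 |
| 0.85 | 0.840 | 0.419 | 1.3 |
| 0.90 | 0.880 | 0.535 | 1.7 |
| 0.98 | 0.944 | 0.758 | 2.4 |

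**4. Does a hold-out inside Aim 2 reveal it?** This was simulated with every input assumed: 6,000 patients, feature prevalence 30%, log odds ratio 1.2 for the feature, 80% scored in-sample, and out-of-sample sensitivity and specificity of 0.80. The outcome models were fitted on 80% of the cohort. The AUC gain from the AI class was measured in the remaining 20% and in new patients.

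| In-sample accuracy | AUC gain, held-back cohort patients | AUC gain, new patients |
|---|---|---|
| 0.80 | 0.027 | 0.028 |
| 0.90 | 0.041 | 0.027 |
| 0.99 | 0.062 | 0.025 |

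With no train-test gap the two columns agree. With a gap, the held-back patients show the inflated gain, so validation within Aim 2 does not expose it.

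**The case against.** The strongest reply is that the article does not say how VOTOR patients are scored. Fig 1, to which it refers for the analysis plan, is not available here, and out-of-fold scoring could sit there or in a fuller plan. That is fair, and a bare missing detail would be no finding. But the article does state the components: VOTOR cases in training, only 20% of pairs kept out, outputs for VOTOR cases carried forward without restriction. It also states its response to Aim 1 error, and that response is inadequate whatever Fig 1 holds.

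A second reply is that the sentence speaks of reviewing performance and does not claim to correct anything. This is right as to wording. It is still the only response offered to an error the authors themselves raise.

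Several stronger readings are tempting and are not supported:

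- *Outcome leakage.* The network learns fracture and treatment characteristics, not the Aim 2 outcomes.
- *That 80% is a stated figure for VOTOR patients.* It is inferred from the hold-out of pairs, and the range in the working applies.
- *That inflation is certain or about twofold.* Its direction and size depend on a train-test gap and on label quality, neither of which is given. The Introduction reports random classification error in coding and between observers, and fitting noisy labels more closely need not bring predictions closer to the true fracture.
- *That 0.80 is the plan's target sensitivity.* It appears only as the alternative hypothesis for the agreement sample; neither sensitivity nor specificity is named.
- *That the error would be expensive to undo after linkage.* Nothing in the text bears on that cost.

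**Conclusion.** The point holds in a limited form. Followed as written, most Aim 2 patients would carry in-sample AI indicators whose error differs from that in new patients, and accuracy, precision and recall on those indicators can neither show nor remove the difference. If the network fits its training patients better than new ones, the estimated gain from the AI variables is likely to exceed the gain on deployment.

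The size cannot be derived from the document. The ratios in the working are illustrations on the R-squared scale. They rest on assumed accuracies, equal sensitivity and specificity, a proportional split by patient, and a feature independent of the registry covariates. They should not be read as an expected bias for the measures that the plan names. This should be changed before the AI outputs are generated for Aim 2; confidence is medium because of the unseen figure and the unknown train-test gap.

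**What to change.** Split by patient, not by pair, and generate the AI indicators by K-fold cross-fitting (K = 5, for example), so that each VOTOR patient is scored by a network that never saw that patient. Use these out-of-fold probabilities and classes as the Aim 2 predictors. The cost is about K times the training compute; no new data or readers are needed.

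As a minimum alternative, carry a held-out flag into the linked data and quantify the AI gain only in patients kept out of network training. That leaves about 1,200 VOTOR cases under a proportional split, but anywhere from 0 to 2,000 otherwise, so the hold-out should be stratified by source. The cost is wider intervals.

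The performance measures can stay, but not as the sole response to Aim 1 error. If Fig 1 or a fuller plan already provides out-of-fold scoring, a sentence in the Aim 2 section saying so would settle the point.

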#### 1) VOTOR registry data

The VOTOR registry is the largest and most comprehensive orthopaedic trauma outcomes registry worldwide and is compliant with the ACSQHC operating principles for clinical quality registries. For patients hospitalised >24h for their wrist fracture, cases will be identified through VOTOR using the relevant ICD-10-AM diagnosis codes for the admission. Demographic, injury event, injury diagnosis (ICD-10-AM), procedures (ACHI), in-hospital outcomes, limited implant data, X-ray images, text reports from radiology and surgery, and patient-reported outcome measures (PROMs) will be extracted for all eligible patients for this study. The PROMs are collected prospectively via telephone interview at 6-, 12- and 24-months post-injury [34], and include the 12-item World Health Organization Disability Assessment Schedule (WHODAS), 5-level EQ-5D (EQ-5D-5L), numerical rating scale for pain, pain location, return to work and work disability questions. Follow-up rates exceed 80% at each time point. Linkage with the Victorian Registry of Births, Deaths and Marriages (VBDM) is used to identify post-discharge deaths.

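### Accuracy, precision and recall are fixed for all Aim 2 models, but precision and recall cannot be computed for the EQ-5D-5L, WHODAS and pain scores

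*Protocol article*

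**What the plan says.** In the Protocol article, the section Aim 2: Prediction modelling lists two kinds of outcome. One kind is events: five fracture management complications, readmission, and ED presentation. The other is patient-reported outcomes at 6, 12 and 24 months: EQ-5D-5L, 12-item WHODAS, pain scores, return to work and work disability. The section on VOTOR registry data describes the pain item and its neighbours as "numerical rating scale for pain, pain location, return to work and work disability questions". Neither section gives a cut-point for any score.

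The named methods include "Linear and generalized linear mixed models (LMMLasso/GLMMLasso) [45" and "longitudinal support vector regression (LS-SVM) [47] and mixed effects random forest (MERF) [48". The article then notes that error from Aim 1 may carry into the Aim 2 models, "so we will use several measures to review model performance". The measures are given in the next sentence: "All models will be summarised by the predictive performance measures of accuracy, precision and recall [49". Their purpose follows in the same sentence: "to select the best performing model for each outcome, and quantify the impact of the inclusion of the AI variables over registry data alone".

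**The concern.** Aim 2 asks whether AI-derived characteristics improve prediction over registry data alone. One sentence of the article sets how that is judged, and it covers every model and every outcome. If its measures cannot be calculated for the score outcomes, the plan has no usable rule for choosing a model or stating the AI gain for health status, disability and pain.

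The analyst would then have to choose other measures after the plan is fixed, or categorise the scores at a threshold of their own choosing. The first leaves the comparison unspecified. The second discards information and leaves the result open to the choice of cut-point.

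There is a lesser concern for the binary outcomes. All three measures depend on a classification cut-off that the article does not state, and none shows whether predicted risks agree with observed risks.

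**Working it through.** **1. The plan's own figure.** The only calculated figure is for Aim 1: "A random sample of 517 patient sets of X-ray and radiology reports", from a "null hypothesis of 0.7, alternative hypothesis of 0.8, power>0.8 and prevalence of dorsal displacement type fractures of 30" per cent. An exact one-sample binomial test of 0.7 against 0.8, two-sided 5% (assumed, as alpha is not stated), needs 155 positive cases (power 0.818). Then 155 / 0.30 = 516.7, so 517. It reproduces. It has no bearing on this point, because no figure is attached to the Aim 2 measures.

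**2. Do the measures fit the outcomes?** With counts of true and false positives and negatives:

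- recall = TP / (TP + FN)
- precision = TP / (TP + FP)
- accuracy = (TP + TN) / N

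Each needs a predicted class and an observed class.

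| Aim 2 outcome | Class defined in the article? | Computable as stated? |
|---|---|---|
| Complications, readmission, ED presentation | Yes (event or no event) | Yes, once a cut-off is set |
| Return to work | Naturally categorical | Yes, once a cut-off is set |
| EQ-5D-5L, 12-item WHODAS, pain scores | No cut-point given | No, unless categorised |

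Linear mixed-model lasso and support vector regression predict a continuous value, so the article evidently intends continuous prediction for at least some outcomes.

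**3. What categorising would cost.** For a normal score split so that a proportion p lies on one side, the relative efficiency is φ(z_p)² / [p(1 − p)].

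- p = 0.5: 0.3989² / 0.25 = 0.637
- p = 0.3: z = −0.524, φ = 0.3477, and 0.3477² / 0.21 = 0.576

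A median split therefore behaves like discarding about 36% of the patients (1 − 0.637), and a 30/70 split about 42% (1 − 0.576). This assumes normality. The article states no split.

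**4. Binary outcomes (conditional illustration).** The article gives no event rates and no cut-off, so both are assumed. Risk scores are taken as N(0,1) without the event and N(d,1) with it, where d = √2 · Φ⁻¹(AUC).

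*Cut-off at predicted risk 0.5, event rate 2%.* The likelihood ratio must reach 0.98 / 0.02 = 49, so the threshold is x = d/2 + ln(49)/d.

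- AUC 0.75: d = 0.954, x = 0.477 + 4.080 = 4.557, recall = 1 − Φ(3.603) = 0.00016, accuracy 0.980
- AUC 0.65: d = 0.545, x = 0.272 + 7.142 = 7.414, recall essentially 0, accuracy 0.980

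Predicting no event for everyone also gives 0.980.

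*Midpoint (Youden) cut-off, x = d/2, same rate.* Recall and specificity both equal Φ(d/2), so accuracy has the same value.

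- AUC 0.65: recall and accuracy 0.607; precision = 0.02 × 0.607 / (0.02 × 0.607 + 0.98 × 0.393) = 3.1%
- AUC 0.75: recall and accuracy 0.683; precision = 0.02 × 0.683 / (0.02 × 0.683 + 0.98 × 0.317) = 4.2%

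*Range over event rates, AUC 0.70 to 0.80, cut-off 0.5:*

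| Assumed rate | Accuracy | Recall | Accuracy of predicting no event |
|---|---|---|---|
| 2% | 98.0% to 98.0% | 0.0% to 0.4% | 98% |
| 5% | 95.0% to 95.05% | 0.0% to 3.0% | 95% |
| 10% | 90.0% to 90.4% | 0.5% to 10.5% | 90% |
| 30% | 72.0% to 76.9% | 22.0% to 45.4% | 70% |

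Whether these measures register a real gain thus depends on the event rate and on a cut-off not yet stated.

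**The case against.** The other side has several fair points.

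- **A condensed article.** Fig 1, which outlines the analysis for Aims 1 and 2, is not shown in the text reviewed, and the article promises several measures. This lowers certainty about the full plan. It does not change the sentence itself, which covers all models and each outcome and names only these three.
- **Other readings.** Accuracy can loosely mean prediction error, and EQ-5D-5L could be analysed by its levels. The article says neither. Precision and recall have no such loose reading for a score.
- **Cut-offs belong in an analysis plan.** This stands. The absence of a cut-off for the binary outcomes is no finding.

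Some stronger conclusions are tempting but unsupported.

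- A reader might infer that gains for rare complications will be hidden. That holds at an assumed 2% rate and 0.5 cut-off. At the midpoint cut-off all three measures show the gain.
- A reader might infer that none of the measures reflects discrimination. Recall is sensitivity and precision is positive predictive value. Both reflect discrimination at a threshold.
- A reader might infer that the AI gain will be optimistic because the same measures choose the model and quantify the gain. The article does not say that both steps use the same data, and resampling design is commonly left to the full plan.
- A reader might count nine undefined outcomes (three scores at three times). With longitudinal models, three outcomes is an equally fair reading.

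**Conclusion.** The sentence is wrong as written for the score outcomes. Precision and recall cannot be calculated for EQ-5D-5L, WHODAS and pain scores without a categorisation that the article does not give, yet they are part of the stated rule for choosing the model and stating the AI gain. This conclusion rests on the text alone and needs no assumed rate.

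If the scores were split in order to comply, relative efficiency would be about 0.64 at a median split and 0.58 at 30/70, assuming normality. These figures describe the cost of one way out, not a step the plan states.

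For the binary outcomes the three measures are usable but incomplete: they depend on a threshold and do not assess calibration. The size of any masking is conditional on the assumed rate and cut-off. It ranges from complete (2%, cut-off 0.5) to none (2%, midpoint cut-off).

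**What to change.** Replace the sentence with measures by type of outcome:

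- **EQ-5D-5L, WHODAS and pain scores:** out-of-sample RMSE or MAE, R-squared and calibration.
- **Binary outcomes:** keep precision and recall at a stated cut-off, and add AUC, Brier score and calibration.
- **AI effect for every outcome:** the paired difference with minus without the AI variables, in the same patients, with a confidence interval.

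It would also be good practice to state that this difference is estimated outside the data used to choose the algorithm. The article does not show that the plan does otherwise, so this is a clarification and not a correction.

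The cost is plan wording and routine analysis code. No new data are needed. If nested resampling is used, it adds computing time.
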